### Recruitment

Potential participants will be identified at the weekly multidisciplinary, upper gastrointestinal cancer meetings by a team member involved in the patient’s care. At the surgical clinic potential participants will asked by a member of the healthcare team whether they are happy to receive information about the study. If they agree they will be provided with a participant information leaflet either by a member of the research team (if available) or the clinical team, and asked to give their consent for a member of the research team to contact them by telephone. A minimum of 24 hours later a member of the research team will contact the potential participant by telephone. If they agree to take part they will be visited in hospital at their pre-assessment clinic appointment. Those patients who do not wish to be contacted by telephone can inform their clinician that they wish to take part or telephone the research team.

Potential participants for the qualitative exploratory study will be those recruited into the RCT and their carers. At the initial recruitment stage participants will be asked to indicate on the consent form if they agree to be interviewed. Following the six-week intervention period, potential participants will be contacted and invited to be interviewed. Where a partner or main carer is identified, they too will be asked if they are interested in participating. On agreement, a volunteer information sheet will be posted out and consent will be taken prior to the interview taking place. It is envisaged that including the partner or carer will add to the depth of information, particularly regarding experiences of home tube feeding. The sample will also include male and female patients without family or support at home. Participants will be given the option to be visited at home or to attend the hospital for interview. Recruitment to the study will be conducted over a 20-month-period and individual participation in the study will last for 7 months.

### Sample size

Home JEJ feeding is not routinely carried out at present and there is no published data on the variables of interest in this patient population. Consequently the sample size in this pilot study was chosen to enable a sensible estimation of the quantities of interest, in particular variability, whilst not exposing too large a number of participants to the full range of experimental procedures.

We therefore aim to recruit 60 subjects, 30 randomized to home JEJ and 30 to treatment-as-usual, which (allowing for up to 17% early withdrawal) would result in 50 participants completing the 6-week intervention period.

### Randomization

Participants are randomized to either the control or intervention group at enrolment, and prior to surgery, so that baseline QoL and nutritional parameters can be collected. We anticipate an early withdrawal rate due to perioperative mortality or morbidity of around 5% based on local experience. At the time of the operation it may not be clinically suitable to place a JEJ tube in all subjects, or some will not have a functioning JEJ tube (approximately 2%, due to kinking or blockage).

The randomized schedule is managed by the University of Leicester Clinical Trials Unit, using computer generated random assignment, using permuted block randomization, stratified for type of procedure (esophagectomy or total gastrectomy). A member of the research team (dietitian or lead clinician) will randomize the participant through an electronic Interactive Web Response System (IWRS). Participants are sequentially assigned to groups as they are entered into the study and the IWRS will provide a trial participation number.

Neither the study participants nor the research team are blinded to the allocation group. However the research dietician has no role in determining clinical care unless there are patient safety concerns. The research team did not consider it either ethical or practical to administer placebo feed to the control group.

### Standard postoperative care

All participants will receive standard postoperative care whilst in hospital, consisting of feeds via a JEJ tube placed at the time of surgery. Tube insertion, commencement of feeds, and subsequent increase in volume will follow normal clinical care (Figure 1).

**Figure 1 F1:**
[figure not shown]
Plan for jejunostomy (JEJ) feeds in hospital (routine care) and post-discharge (intervention and control groups).

Continuous JEJ feeds will be reduced to supplementary overnight feeds (10 to 15 hours duration) when oral intake starts (at approximately postoperative day 7) and continue until the morning of the day of hospital discharge in all participants. Dietary advice, including food fortification and the use of prescribed nutritional supplements, with supporting written information will be provided to all subjects by the clinical team prior to discharge.

### Intervention

Participants will be referred to the Home Enteral Nutrition Service (HEN) and they will be taught (with or without family support) to independently manage the JEJ feed at home. For the first six weeks after discharge from hospital, the participant and/or carer will be trained to administer overnight jejunostomy feeds via an electronic feeding pump. The timings of feeds will be decided in conjunction with the participant’s normal and expected routine following discharge home. The participant’s individual nutritional requirements will be assessed using prediction equations [23,24] aiming to provide at least 50% of energy and protein needs via the JEJ feed. The final amount provided for each subject will be adjusted depending on the oral intake and weight change as assessed by the Home Enteral Nutrition Service Dietitian (HEN).

Post-discharge dietetic follow-up will involve a routine telephone call and home visit from HENs within the first week of discharge and additional HEN input will be dictated by nutritional need but will include at least one further contact within the six-week intervention period. It may be necessary to reduce the rate and amount of JEJ feed the participant receives to effectively manage complications (gastrointestinal intolerance). The initial adjustments will be to reduce the feed rate by 10 – 25 ml/hr, keeping the total volume of feed delivered the same, but infused over a longer period (for example 100 ml/hr over 10 hours reduced to 80 ml/hr over 12.5 hours. The second step will be to adjust the feed composition (e.g. if the participant is experiencing an alteration in bowel habit, fibre will either be reduced or increased depending on the content of the current feed). If these steps do not effect an improvement, the total amount of energy provided by the feed will be reduced (temporarily). JEJ feeds will only be stopped completely after discussion with the Healthcare Team.

### Control

Participants randomized to the control group will continue to receive routine clinical care: JEJ feeds will be discontinued on day of discharge, the JEJ tube will remain in place until outpatient review in week six, and prior to discharge the participants will be taught how to flush the JEJ tube daily. Post-discharge dietetic follow-up will involve a routine telephone call and home visit from HENs within the first week of discharge. Additional HEN input will be dictated by nutritional need but will include at least one further contact within the six-week study period.

Following standard practice it may be considered necessary by the healthcare team to re-commence JEJ feeds which we anticipate may be the case in up to 15% of the control group. The criteria for recommencement of the feed will include the following: (1) more than 5% weight loss from baseline or hospital discharge value (visits 1 or 2), (2) clinical assessment by the managing team based on functional status (worsening dysphagia, exhaustion, or anorexia), or (3) oral energy intake reduced to one third of the estimated requirements.

In these situations, JEJ feeds will be restarted according to current practice (if necessary the patient will be readmitted to hospital). The trial participant will continue to be monitored following the trial schedule and the results will be analyzed on both an intention-to-treat and perprotocol basis. The only difference between the intervention and control arms will be the management and administration of the supplementary JEJ feeding for six weeks. All participants will receive clinical reviews following routine care from the multi-disciplinary team (MDT). It is likely that a small number of patients randomized to either group will require home jejunostomy feeding as part of their routine clinical care. These patients will continue feeding in accordance with their planned care. Consideration will be given to withdrawing the participant from the study where there has been major protocol deviation.

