## Outcome measures

### Quantitative data

The primary outcome measures in this pilot study have been chosen to determine whether or not an appropriately powered definitive trial will be possible. To this effect, the primary outcome measures are recruitment and retention rates at six weeks and six months post-baseline. Additional measures to be recorded at discharge, six weeks, three months and six months after baseline focus on the nutritional status and quality of life, specifically (1) nutritional parameters of weight, body mass index, upper arm anthropometry, and grip strength, (2) nutritional intake to include total energy (kcal/d) and protein intake (g/day), contribution of oral intake (food, fluids), oral nutritional supplements, and JEJ feed, (3) postoperative complications, (4) QoL using the European Organization for Research and Treatment of Cancer (EORTC) generic cancer questionnaire (QLQ-C30)[25] and the EORTC disease specific (esophagogastric) questionnaire (QLQ-OG25) [26].

To enable preliminary assessment of cost-effectiveness, QoL using the five domain EuroQol health outcome instrument (EQ-5D) [27] will be measured at three and six-months post-baseline and healthcare costs will be recorded for the duration of the study period. Survival data will also be collected at 12-months post-surgery.

Adverse events and serious adverse events will be defined in accordance with both the Medicines for Human Use (Clinical Trials) Regulations 2004 (SI2004/1031) and the subsequent amendment regulations (SI2006/1938) and ICH-GCP. Expected adverse events associated with the jejunostomy tube are blockage of the tube or inadvertent removal of the tube rendering feeding impossible and skin infection around the tube. Expected adverse events associated with the feed are bloating and diarrhoea.

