## Data analysis

### Quantitative data

As this is a pilot study and we aim to estimate a number of quantities necessary for the design and delivery of a definitive multi-centre trial, the estimates calculated will be presented along with 95% confidence intervals where appropriate. The proportion of eligible patients who consent to participate in the pilot will be calculated, along with the proportions in each intervention group completing six weeks and six months of assessments. Hospital readmission rates will be presented by intervention group. Variability of the QoL measures will be calculated, both by each group and pooled across both groups.

As it is anticipated that the likely outcome measure for the multi-centre trial will be QoL, a comparison of the QoL measure EORTC QLQ-C30 will be conducted using the Students t-test to compare the mean between the groups to provide a preliminary estimate of the treatment effect. Distribution of the data will be assessed graphically and if the normality assumption is considered to be unreasonable a non-parametric approach will be taken. A secondary analysis, using analysis of covariance (ANCOVA) and regression models will be conducted to adjust for type of surgery (used as a stratification factor in randomization) and baseline value of EORTC QLQ-C30.

The findings of the qualitative research may lead to a different outcome measure being proposed as the primary in the definitive trial and consequently the other QOL measures and other continuous outcomes at six weeks, three months, and six months will be analyzed similarly.

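### The option to withdraw participants from the study for a major protocol deviation works against the promised follow-up, the intention-to-treat analysis and the primary retention outcome

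*Protocol article*

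**What the plan says.** All the rules on departures from allocated feeding stand in the last two paragraphs of the Control section.

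- For controls, the healthcare team may "re-commence JEJ feeds which we anticipate may be the case in up to 15% of the control group", against listed criteria.
- For those participants the section says: "The trial participant will continue to be monitored following the trial schedule". Both an intention-to-treat and a per-protocol analysis are promised.
- It then widens to both arms: "It is likely that a small number of patients randomized to either group will require home jejunostomy feeding as part of their routine clinical care". Their feeding goes on as planned in their care. Nothing is said about their trial follow-up.
- The section closes with: "Consideration will be given to withdrawing the participant from the study where there has been major protocol deviation".

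Under Outcome measures, "the primary outcome measures are recruitment and retention rates at six weeks and six months post-baseline". Under Data analysis, the quantity to be calculated is "the proportions in each intervention group completing six weeks and six months of assessments". The Randomization section states that neither participants nor the research team are blinded.

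**The concern.** Stopping or changing the allocated feeding and leaving the study are different events. Intention-to-treat analysis needs outcomes from people who departed from their allocation. In its ordinary meaning, withdrawal from the study ends the later assessments, so those outcomes are lost.

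Three things follow if the closing sentence is used.

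1. **Selective loss of data.** The choice is discretionary and made with knowledge of the arm and the clinical course. People who depart from allocation are unlikely to be a random subset, so comparisons of quality of life, weight and readmission could be biased.
2. **An incomplete intention-to-treat analysis.** The data after the deviation would be missing because of a decision by the study, not because the participant was unwilling.
3. **A mixed primary outcome.** A withdrawn participant does not complete the assessments and so counts as not retained. The pilot is meant to show whether a definitive trial is possible. A retention rate that combines patient-initiated loss with team-initiated removal is hard to carry forward to that trial.

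The sentence also gains nothing analytically. A per-protocol analysis is already planned, and it can set deviators aside without ending their follow-up.

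**Working it through.** **Comparison of the text**

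| Group | Stated follow-up | Reached by the withdrawal sentence? |
|---|---|---|
| Controls restarted on feeds under the listed criteria | Stay on schedule; both analyses | Not excepted in words; kept on the natural reading |
| Either arm, home feeding as routine care | Feeding continues; trial follow-up not stated | Open; the withdrawal sentence comes directly after |
| Any other major deviator | Not stated | Yes; no number given |

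**Inputs**
- Sample size section: 60 participants, 30 per arm; up to 17% early withdrawal; 50 completing six weeks.
- Randomization section: about 5% perioperative early withdrawal; about 2% without a functioning tube.
- Control section: feeds restarted in up to 15% of controls.

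**The plan's own figure.** 60 × (1 − 0.17) = 49.8, which rounds to 50. Equivalently, 10/60 = 16.7%. The stated figure reproduces.

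**Illustration.** Assume that the 50 completers split equally (25 per arm), that those withdrawn would otherwise have been retained, and that the withdrawals are not already inside the 17%. With x controls withdrawn, control retention = (25 − x)/30 and overall retention = (50 − x)/60. Each withdrawal costs 1/30 = 3.3 points in the control arm and 1/60 = 1.7 points overall. The protocol's restart ceiling is 0.15 × 30 = 4.5 controls. Intervals are exact (Clopper-Pearson) 95% limits.

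| Controls withdrawn | Control retention (95% CI) | Overall retention (95% CI) |
|---|---|---|
| 0 | 25/30 = 83.3% (65.3 to 94.4) | 50/60 = 83.3% (71.5 to 91.7) |
| 1 | 24/30 = 80.0% (61.4 to 92.3) | 49/60 = 81.7% (69.6 to 90.5) |
| 4 | 21/30 = 70.0% (50.6 to 85.3) | 46/60 = 76.7% (64.0 to 86.6) |

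The row for four, close to the 15% ceiling, shows scale only. It would apply only if restarted controls were treated as major deviators.

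**Room inside the allowance.** 17% − 5% − 2% = 10 percentage points are not itemised. The article does not say whether they already cover withdrawals of this kind. If they do, some or all of the fall shown would be double counting.

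**The case against.** The strongest reply is that the protocol already protects the people most likely to cross over. Restarting feeds in a control is foreseen, has criteria, and is followed by an express promise of continued monitoring. A specific instruction should prevail over a general closing sentence. Likewise, the Intervention section sets out steps for intolerance, up to stopping feeds after discussion with the healthcare team, and nothing calls these deviations. This part stands. A reader might infer that every rescued control would be withdrawn and that control retention would fall accordingly. The documents do not support that.

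A reader might also use the 15 to 20% local rescue rate from the Background. The trial's own expectation is up to 15% of controls, so that range goes beyond what the plan assumes.

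It can further be said that intention-to-treat analysis would not become impossible. That is fair: data collected before withdrawal remain usable in the allocated arm, and the article does not say what is collected afterwards. The analysis would be incomplete.

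Finally, the sentence only permits withdrawal, this is an estimation pilot with no retention threshold, and a fuller document may define a major deviation. The absence of a definition is therefore not the point made here. But a definition alone would not reconcile study-level withdrawal for a deviation with intention-to-treat analysis. Discretion does not help either, because case-by-case removal by an unblinded team makes the retention rate harder to interpret.

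**Conclusion.** The concern holds as an inconsistency in a stated rule. The Control section promises continued follow-up and intention-to-treat analysis for restarted controls, then permits withdrawal from the study for a major deviation, without excepting the home-feeding crossover described just before. Any such withdrawal enters a primary outcome as non-retention.

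Its size is not fixed by the documents. It could be zero if the option is never used. It cannot be put at the number of rescued controls, because on the natural reading they stay in follow-up, and no figure is given for other deviators. The 3.3 points of control retention per withdrawn control rest on the three assumptions stated with the illustration: an equal split of completers, participants who would otherwise have been retained, and losses outside the 17% allowance. The direction of any bias in the outcome comparisons cannot be established from the text.

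**What to change.** Delete the closing sentence of the Control section. In its place, state that a deviation from allocated feeding, in either arm, does not end follow-up, and that deviations are used only to define the per-protocol set.

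Keep retention as the proportion completing assessments. Counting only participant-initiated loss would redefine the primary outcome and flatter it. Beside the rate, report by arm the number of deviations, with deaths, participant-initiated withdrawals and any investigator-initiated withdrawals shown separately. Recruitment began in July 2012, so list any withdrawal already made under this sentence by arm, with its date and reason.

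The cost is one sentence removed, one added, and a few rows in the participant-flow table. The assessments are already scheduled and the per-protocol analysis is already planned. No visit is added, and no feeding rule or clinical decision changes.

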### Qualitative protocol

For those participants recruited into the qualitative exploratory study, face-to-face semi-structured interviews, will be conducted. The aim of this part of the study is to explore the experiences of people with upper gastrointestinal cancer and their carers regarding home jejunostomy feeding. Initially, purposive sampling will be adopted to ensure an appropriate selection of cases. The interviews will all follow the same semi-structured format which encourages exploration and discussion of the following areas: experiences of home enteral feeding, ability to comply with the feeding regimen, ability to care for the JEJ tube, impact on activities of daily living, experiences of eating and concerns over oral intake and nutritional status.

This part of the study requires recruitment of a maximum of 20 participants and their carers or partners.

## Outcome measures

### Quantitative data

The primary outcome measures in this pilot study have been chosen to determine whether or not an appropriately powered definitive trial will be possible. To this effect, the primary outcome measures are recruitment and retention rates at six weeks and six months post-baseline. Additional measures to be recorded at discharge, six weeks, three months and six months after baseline focus on the nutritional status and quality of life, specifically (1) nutritional parameters of weight, body mass index, upper arm anthropometry, and grip strength, (2) nutritional intake to include total energy (kcal/d) and protein intake (g/day), contribution of oral intake (food, fluids), oral nutritional supplements, and JEJ feed, (3) postoperative complications, (4) QoL using the European Organization for Research and Treatment of Cancer (EORTC) generic cancer questionnaire (QLQ-C30)[25] and the EORTC disease specific (esophagogastric) questionnaire (QLQ-OG25) [26].

To enable preliminary assessment of cost-effectiveness, QoL using the five domain EuroQol health outcome instrument (EQ-5D) [27] will be measured at three and six-months post-baseline and healthcare costs will be recorded for the duration of the study period. Survival data will also be collected at 12-months post-surgery.

Adverse events and serious adverse events will be defined in accordance with both the Medicines for Human Use (Clinical Trials) Regulations 2004 (SI2004/1031) and the subsequent amendment regulations (SI2006/1938) and ICH-GCP. Expected adverse events associated with the jejunostomy tube are blockage of the tube or inadvertent removal of the tube rendering feeding impossible and skin infection around the tube. Expected adverse events associated with the feed are bloating and diarrhoea.

Due to the nature of the surgery, it is anticipated that up to 50% of the trial participants will experience a serious adverse event prior to discharge from hospital (after randomization, but before any trial treatment has been administered). These adverse events will be recorded for scientific rigor but will not be reportable to the study sponsor. These include death, return to the operating theatre, return to the intensive care unit for re-ventilation, prolonged ventilation (over 72-hours duration) and pneumonia. Table 1 details the planned visit schedule, including acceptability in the timing of visits and measurements. Assessments will either be carried out at the hospital to coincide with routine clinic visits or at home, depending on participant preference.

**Table 1 T1:** Summary of visit schedule and assessed parameters at each time point

